6.3.10 PK Studies

Refer to section 10.2 for information pertaining to the PK studies.

6.3.11 Self-Reported Adherence

Adherence to all study medications will be assessed by self-report as outlined in the Schedule of Events.

# 7.0 CLINICAL MANAGEMENT ISSUES

Criteria for subject management, dose interruptions, modifications, and discontinuation or changes in study drug treatment will be mandated only for toxicities attributable to RAL. Toxicities due to FTC/TDF should be managed according to standard clinical practice, with the exception of sections 7.9 and 7.10, with the goal of maintaining continuous therapy, if possible. If any individual study drug must be interrupted or discontinued due to toxicity, then the entire regimen also must be interrupted or discontinued.

The grading system for drug toxicities is located in the Division of AIDS Table for Grading the Severity of Adult and Pediatric Adverse Events (DAIDS AE Grading Table), Version 1.0, December 2004, located at the DAIDS RCC Web Site: http://rcc.tech-res.com/tox_tables.htm.

NOTE: The core team must be notified by e-mail regarding toxicities that result in a change in regimen or discontinuation ([[contact]](mailto:[contact])). Team notification regarding toxicity is especially important during the intensive viral sampling phase in the first 2 weeks of treatment. The protocol does not allow drug substitution for toxicity management.

NOTE: Subjects with HIV/HBV co-infection may experience exacerbation of hepatitis B if FTC/TDF is discontinued.  If discontinuation of FTC/TDF is required, liver function should be monitored closely with both clinical and laboratory follow-up.

## 7.1 Grade 1 or 2 Toxicity

Subjects who develop a Grade 1 or 2 AE or toxicity may continue RAL. If subjects choose to discontinue RAL, the site should complete the premature discontinuation of study medications evaluations, notify the A5248 core team, and encourage the subject to continue to attend all study visits for the duration of the study.

## 7.2 Grade 3 Toxicity

If the investigator has compelling evidence that the AE has NOT been caused by RAL, dosing may continue. Subjects who develop possible RAL-related Grade 3 AEs or toxicities, except as defined in the section 7.0, should have their regimen stopped and the A5248 core team must be consulted. The subject should be reevaluated closely until the AE returns to Grade ≤ 2, at which time their regimen may be reintroduced at the discretion of the investigator or according to standard practice.

If the same Grade 3 AE recurs within 4 weeks, the regimen must be permanently discontinued. If the same Grade 3 AE recurs after 4 weeks but is not thought to be related to RAL, the management scheme outlined above may be repeated.

Subjects experiencing Grade 3 AEs requiring permanent discontinuation of the regimen should be followed closely for resolution of the AE to grade ≤ 2 and the core team must be consulted.

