Two phase III randomized controlled trials of treatment-experienced subjects have been reported. These studies, BENCHMRK 1 and 2, were conducted in Europe, Asia/Pacific, Peru, and North and South America.(13;14) In these studies, triple-class resistant subjects were randomized 2:1 to RAL 400 mg BID or placebo plus optimized background therapy (OBT). Results showed that 77% and 43% of subjects in the RAL and placebo arms, respectively, had plasma HIV-1 RNA < 400 copies/mL, with a 2 log10 copy/mL reduction in the RAL-treated subjects. CD4+ T-cell response was also significantly higher in the RAL than the control group. Overall there was no difference in the clinical or laboratory toxicity between those receiving OBT with RAL than with placebo. Drug-related clinical AEs were reported in >5% of subjects receiving RAL in BENCHMRK 1 for diarrhea (6.5%), with this occurring in 11% of controls. In BENCHMRK 2, clinical AEs occurring in >5% of RAL-treated subjects included diarrhea (12.2% versus 9.2% of controls), nausea (9.1% versus 8.4% of controls), and headache (7.8% compared to 4.2% of controls). Laboratory abnormalities reported in >5% of the RAL-treated subjects in BENCHMRK 1 included LDL >190 mg/dL (6% versus 2.8% controls), triglycerides >750 mg/dL (5.6% versus 2.5% controls), aspartate aminotransferase (AST) between 2.6 and 5.1 times upper limit of normal (ULN) (9.9% compared to 2.5% of controls), and alanine aminotransferase (ALT) >5.1 times ULN (5.6% compared to 2.5% of controls). In contrast, for BENCHMRK 2 such laboratory abnormalities were only seen at >5% of individuals for AST between 2.6 and 5 times ULN (8.6% compared to 7.6% of controls) and ALT 2.6 to 5.0 times ULN (6.5% versus 9.2% of controls).

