Gilead Sciences has developed Truvada®, a product containing FTC 200 mg and TDF 300 mg in a fixed dose combination (FDC) tablet formulation. A New Drug Application for the FDC was filed with the U.S. FDA on March 12, 2004, and was approved on August 2, 2004.

Several studies have assessed the safety and efficacy of FTC with TDF, albeit none using FDC. Study M02-418 was a phase III, randomized, open-label, multicenter study designed to compare LPV 800 mg/RTV 200 mg QD vs. LPV 400 mg/RTV 100 mg BID with the background regimen of FTC 200 mg QD and TDF 300 mg QD in ARV-naïve subjects with plasma HIV-1 RNA >1,000 copies/mL.(35) A total of 190 subjects between the ages of 19-75 years were enrolled; 115 to the QD arm and 75 to the BID arm. At week 48, based on the intent-to-treat (ITT) (NC=F) analysis, 70% of subjects in the QD regimen demonstrated plasma HIV-1 RNA <50 copies/mL, compared to 64% of those in the BID group (95% CI: -7%; 20%). Gastrointestinal AEs were the most common cause for discontinuation. Overall, the most common AEs (> 3%) reported were diarrhea, nausea, and vomiting, with diarrhea being reported significantly higher in the QD group (16% vs. 5%; p=0.04). The most common grade 3/4 laboratory abnormalities (> 3%) reported were increased ALT (> 5 x ULN), AST (> 5 x ULN), triglyceride (> 750 mg/dL), and amylase (> 2 x ULN) levels; no significant differences between the 2 groups were observed.

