6.3.7 Laboratory Evaluations

Record all protocol-required laboratory values, regardless of grade, obtained at screening, pre-entry and entry on the CRFs. After entry, record all laboratory values Grade >3 on the CRFs. Any laboratory values that lead to a change in study treatment, regardless of grade, will be recorded on the CRFs.

Sites must refer to the Division of AIDS Table of Grading the severity of Adult and Pediatric Adverse Events (DAIDS AE Grading Table), Version 1.0, December 2004, which can be found on the DAIDS RCC Web site: http://rcc.tech-res.com/tox_tables.htm.

Hematology

The following tests are required and performed in real time at the local laboratory: hemoglobin, hematocrit, white blood cell count (WBC), differential WBC, ANC, and platelet count.

Blood Chemistry

The following tests are required and performed in real time at the local laboratory: electrolytes (Na+, K+, Cl-, HCO3), glucose, creatinine, and blood urea nitrogen (BUN).

Calculated Creatinine Clearance

Calculated CrCl is required as estimated by the Cockcroft-Gault equation (refer to section 4.1.4). This requires the recording of all values of serum creatinine regardless of grade.

Liver Function Tests

The following tests are required and performed in real time at the local laboratory: AST (SGOT), lactate dehydrogenase (LDH), ALT (SGPT), and alkaline phosphatase.

Urinalysis

The urinalysis should be completed as per the Schedule of Events and if clinically indicated. Dipstick or microscopic exam may be done. If dipstick results are abnormal, microscopic exam is required.

Pregnancy Testing

All women of reproductive potential (as defined in section 4.1.5) must have a negative serum or urine beta-human chorionic gonadotropin (-HCG) pregnancy test result at screening and within 48 hours prior to initiating protocol-specified medications and any time thereafter that pregnancy is suspected. (The urine test must have a sensitivity of 25-50 mIU/mL).

Hepatitis B Serology

Documentation of hepatitis B infection status by hepatitis B surface antigen is required prior to study entry. Previous results verifiable by reports from a CLIA-certified laboratory are acceptable any time prior to study entry.

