## 7.3 Grade 4 Toxicity

Subjects who develop a Grade 4 symptomatic AE or toxicity thought to be related to RAL will have their regimen discontinued. If the investigator has compelling evidence that the AE has NOT been caused by RAL, dosing may resume when the AE has resolved to grade ≤ 2.

Subjects experiencing Grade 4 AEs requiring permanent discontinuation of RAL should be followed closely until resolution of the AE to Grade ≤ 2 and the core team must be consulted.

Subjects with Grade 4 asymptomatic laboratory abnormalities in lipids or creatine kinase (CK) may continue RAL.

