## 7.7 AST/ALT Elevations

7.7.1 Grade ≤ 3

The regimen may be continued for asymptomatic, isolated Grade ≤ 3 AST or ALT elevations at the discretion of the site investigator. Careful assessments should be done to rule out the use of alcohol, non-RAL-related drug toxicity, or viral hepatitis as the cause of the Grade 3 elevation.

For symptomatic Grade 3 elevations of AST or ALT, the ARV regimen should be held until toxicity returns to Grade ≤ 2. If symptomatic Grade 3 elevation recurs on rechallenge, the regimen should be discontinued and the core team must be consulted.

7.7.2 Grade 4

The regimen should be held for confirmed asymptomatic AST or ALT Grade 4 elevations until the toxicity returns to Grade ≤ 2. If Grade ≥ 3 elevation in AST or ALT recurs on rechallenge, the ARV regimen should be permanently discontinued and the core team consulted.

Any symptomatic Grade 4 ALT or AST elevation should lead to permanent discontinuation of the ARV regimen if it is suspected to be due to the ARVs. The core team must be consulted.

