9.2.2.4 Safety and Tolerability

- Incidence of Grade 3 and 4 symptoms and laboratory results by body system and by type, excluding asymptomatic elevations in lipids or CK.
- Incidence of permanent discontinuation of study medication for any reason.
- Incidence of permanent discontinuation of study medication for reasons other than virologic failure.
  - - 1. Change in CD4+ T-cell count from baseline to weeks 24, 48, and 72. The baseline CD4+T-cell count will be the arithmetic mean of the two measurements obtained on different days closest before or on the day of study medication dispensation (e.g., pre-entry and entry determinations). If only one such measurement is available, then this measurement will be the baseline value.
      2. RAL-, FTC- and TDF-resistance mutations using very sensitive resistance assay measures in subjects with detectable viremia.
      3. Subject-specific estimates of: (a) the minimum concentration (Cmin) for RAL, FTC, and TDF; (b) viral load changes on day 7; (c) CD4+ T-cell counts changes over days 0-14 (magnitude of changes and estimated slope). The baseline HIV-1 RNA will be the geometric mean of the two measurements obtained on different days closest before or on the day of study medication dispensation (e.g., pre-entry and entry determinations). If only one such measurement is available, then this measurement will be the baseline value.
      4. Adherence by self-report at each study visit.
      5. Total cell-associated proviral DNA, LTR circular DNA, and integrated proviral DNA as measured by an assay currently undergoing validation; and unintegrated linear proviral DNA calculated by subtraction, measured on days 0, 2, 7, 10, 14, 21, 28, and 56; weeks 12, 24, 48, and 72; and at the time of virologic failure.
      6. Plasma HIV-1 RNA levels collected from week 24 through week 72, as quantified by the single copy assay. If enough points are above the lower limit of the single-copy assay, the rate of change over the third (and possibly fourth) phase of viral decay will be estimated.
      7. CD4+ T-cell counts measured on days 0, 2, 7, 10, and 14.

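### Section 7.2 stops the regimen for an asymptomatic Grade 3 lipid or CK abnormality that section 7.3 lets a subject treat through at Grade 4

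*Protocol*

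**What the plan says.** Protocol section 7.2 sets the general rule for Grade 3 events: "Subjects who develop possible RAL-related Grade 3 AEs or toxicities, except as defined in the section 7.0, should have their regimen stopped". The same sentence requires consultation with the core team. The regimen may be restarted once the event is back to Grade 2 or below. On recurrence the wording becomes mandatory: "If the same Grade 3 AE recurs within 4 weeks, the regimen must be permanently discontinued". Dosing may go on without a stop if there is compelling evidence that RAL is not the cause.

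Section 7.3 covers Grade 4. Its discontinuation rule is addressed to symptomatic events thought to be related to RAL, and it ends with an exemption: "Subjects with Grade 4 asymptomatic laboratory abnormalities in lipids or creatine kinase (CK) may continue RAL".

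Section 9.2.2.4 defines the safety endpoint as "Incidence of Grade 3 and 4 symptoms and laboratory results by body system and by type, excluding asymptomatic elevations in lipids or CK".

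Section 7.7 contains a Grade 3 laboratory exemption that is written out: "The regimen may be continued for asymptomatic, isolated Grade ≤ 3 AST or ALT elevations at the discretion of the site investigator".

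**The concern.** A dosing rule should not become more lenient as the same abnormality gets worse. Read literally, a subject whose asymptomatic triglycerides or CK are at Grade 3 and possibly due to RAL should stop. If the value climbs to Grade 4, the subject may carry on. No reason for this is given.

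What is at stake is avoidable interruption of treatment. Under section 7.0, stopping one drug for toxicity stops the whole regimen, and no substitution is allowed. Section 7.0 also warns that stopping FTC/TDF may exacerbate hepatitis B in co-infected subjects, and co-infection is not among the exclusions in section 4.2. An unneeded stop is therefore not free of risk, and a second Grade 3 value within 4 weeks would make it permanent.

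**Working it through.** The plan states no figure on this point, so the check is a comparison of the texts.

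**Step 1. The two rules side by side, for an asymptomatic lipid or CK abnormality judged possibly RAL-related.**

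| | Grade 3 (7.2) | Grade 4 (7.3) |
| --- | --- | --- |
| First occurrence | Regimen should be stopped; core team must be consulted | RAL may continue |
| Recurrence within 4 weeks | Regimen must be stopped permanently | No such rule for these abnormalities |
| Limited to symptomatic events? | No | Yes, in the discontinuation sentence |
| Lipid/CK exemption | None | Yes |

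**Step 2. Whether the exception clause in 7.2 closes the gap.** The clause points to section 7.0.

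- The text directly under 7.0 has no lipid or CK exception.
- If 7.0 stands for the whole chapter, the specific rules are rash (7.4), nausea and vomiting (7.5), diarrhea (7.6), AST/ALT (7.7), lactate (7.8), creatinine clearance (7.9), skin hyperpigmentation (7.10), headache (7.11) and pregnancy. None mentions lipids or CK.
- The only lipid/CK sentence in the chapter is the one in 7.3, and it names Grade 4.

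No reading of the cross-reference therefore yields a stated Grade 3 exemption.

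**Step 3. What the authors probably meant.** Section 9.2.2.4 sets asymptomatic lipid and CK elevations aside at Grade 3 and Grade 4 alike. Section 7.7 shows that when a Grade 3 laboratory finding was meant to be treated through, the grade was named. Together these suggest that the exemption was meant for both grades and that 7.2 lacks the sentence. This is an inference: 9.2.2.4 governs what is counted, not how subjects are dosed.

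**Step 4. How often the rule could apply.** The required panels in section 6.3.7 are hematology, chemistry (electrolytes, glucose, creatinine, BUN), calculated creatinine clearance, liver function tests (AST, ALT, LDH, alkaline phosphatase) and urinalysis. Lipids and CK are in none of them, nor in the Schedule of Events. A case needs a test the protocol does not ask for, a Grade 3 result, no symptoms, and a judgement that RAL is possibly responsible.

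**The case against.** The best defence is that the protocol uses section 7.0 for the whole chapter. Section 9.5 sends subject management there, and so does the toxicity section of the A5249s substudy. On that usage the 7.3 exemption falls within the exception in 7.2, and a sensible reader would conclude that what is tolerated at Grade 4 is tolerated at Grade 3. That is probably the intended meaning. But the reader must supply a step that no sentence states and that runs against the plain instruction in 7.2.

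The safeguards carry more weight. The first stop is worded as should, core-team consultation is mandatory in every such case, restart is allowed, and a permanent stop needs an event, a return to Grade 2 or below, and a recurrence within 4 weeks. This stands and keeps the impact very small.

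Two stronger readings are tempting, and the documents support neither.

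- *A case count.* Section 2.1 reports "triglycerides >750 mg/dL (5.6% versus 2.5% controls") in one phase III trial of RAL. A reader might compute 34 × 0.056 = 1.9 expected cases, or 34 × 0.025 = 0.85 at the control rate. That assumes all 34 subjects are tested, which the protocol does not require. It also takes rates from treatment-experienced subjects with triple-class resistance, whereas these subjects are treatment-naïve. The rates are not restricted to Grade 3, to asymptomatic or to RAL-related cases. The link from that cut-off to Grade 3 or 4 comes from a different trial described in the same section, and the grading table that governs A5248 is only cited. The sister phase III trial is reported with AST and ALT as its only laboratory abnormalities above 5%. No CK rate is given. The product is not a usable estimate or an upper bound.
- *Damage to the primary analysis.* A stop in days 0 to 14 would cost later HIV-1 RNA values under section 9.6.1 and trigger replacement under section 9.1. Nothing in the protocol suggests this would happen often enough to matter, and values before the interruption are kept.

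**Conclusion.** The point holds as a minor inconsistency in a dosing rule. Sections 7.2 and 7.3, taken as written, give the milder lipid or CK abnormality the stricter action, and nothing in chapter 7 states otherwise. Section 9.2.2.4 makes a drafting slip the likeliest explanation.

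The omission itself is certain from the text; that sites would actually stop treatment because of it is not. No protocol-required test would bring a case to light, core-team consultation comes with each one, and no number of affected subjects can be given reliably. No effect on d1, the sample size or any other analysis is claimed. The point concerns a dosing instruction that sites act on, so an analysis plan could not settle it.

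**What to change.** In section 7.2:

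1. Add a Grade 3 counterpart to the exemption in 7.3, for example: *For an asymptomatic Grade 3 laboratory abnormality in lipids or CK, RAL may be continued, and the stopping and 4-week recurrence rules of this section do not apply.*
2. Replace the exception clause that points to section 7.0 with: *except as stated below and in sections 7.4 to 7.11*.

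The second half of the added sentence is needed. The recurrence rule has no exception and no relatedness condition. If only continuation were permitted, a CK value that fell and rose again within 4 weeks could still be read as requiring a permanent stop.

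Leave 7.3 and 9.2.2.4 unchanged. The wording permits continuation and does not require it, so the investigator's judgement is kept. The cost is one sentence and one changed phrase, by clarification memo or with the next amendment.

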## 7.3 Grade 4 Toxicity

Subjects who develop a Grade 4 symptomatic AE or toxicity thought to be related to RAL will have their regimen discontinued. If the investigator has compelling evidence that the AE has NOT been caused by RAL, dosing may resume when the AE has resolved to grade ≤ 2.

Subjects experiencing Grade 4 AEs requiring permanent discontinuation of RAL should be followed closely until resolution of the AE to Grade ≤ 2 and the core team must be consulted.

Subjects with Grade 4 asymptomatic laboratory abnormalities in lipids or creatine kinase (CK) may continue RAL.

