## 7.5 Nausea/Vomiting

Nausea/vomiting may be treated symptomatically with oral antiemetics or antiemetic suppositories. For Grade ≥ 3 nausea and vomiting thought secondary to RAL that fails to improve on antiemetics to Grade ≤ 2, the regimen may be held until Grade ≤ 2. If Grade ≥ 3 nausea and vomiting recurs with reinstitution of RAL or persists beyond 14 days despite symptomatic management, then their regimen may be discontinued at the discretion of the investigator and in consultation with the core team.

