## 7.6 Diarrhea

Symptomatic treatment of any grade diarrhea with oral antidiarrheal drugs is permitted once infectious causes of diarrhea have been ruled out by the site investigator. If Grade ≥ 3 diarrhea thought to be related to RAL persists despite symptomatic management, then the regimen should be held until Grade ≤ 2. If Grade ≥ 3 diarrhea recurs with reinstitution of RAL or persists beyond 14 days despite symptomatic management, then the regimen should be discontinued and the core team consulted.

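### Protocol 7.3 discontinues the regimen for a symptomatic Grade 4 event attributed to RAL, while 7.5 and 7.6 provide for a hold and restart in Grade 4 nausea/vomiting and diarrhea, and no clause says which governs

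*Protocol*

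**What the plan says.** Protocol 7.3 gives the general Grade 4 rule: "Subjects who develop a Grade 4 symptomatic AE or toxicity thought to be related to RAL will have their regimen discontinued". Resumption appears once, for events not due to the drug: "If the investigator has compelling evidence that the AE has NOT been caused by RAL, dosing may resume when the AE has resolved to grade" 2 or lower. The only carve-out is for asymptomatic lipid or CK abnormalities.

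Protocol 7.5 covers nausea and vomiting of Grade ≥ 3 attributed to RAL. For an event "that fails to improve on antiemetics to Grade ≤ 2, the regimen may be held until Grade ≤ 2". If it recurs once RAL is restarted, or lasts more than 14 days despite treatment, "then their regimen may be discontinued at the discretion of the investigator and in consultation with the core team".

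Protocol 7.6 covers RAL-related diarrhea of Grade ≥ 3. If it persists on symptomatic treatment, "then the regimen should be held until Grade ≤ 2". Discontinuation, with core team consultation, follows only on recurrence after restart or persistence beyond 14 days.

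Protocol 7.2, the Grade 3 rule, requires the regimen to be stopped for possibly RAL-related events, "except as defined in the section 7.0". It adds: "If the same Grade 3 AE recurs within 4 weeks, the regimen must be permanently discontinued".

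Protocol 8.1 lists drug-related toxicity as a ground for permanent treatment discontinuation and refers the reader to 7.1-7.3 only. Protocol 9.2.2.4 makes permanent discontinuation of study medication a secondary safety endpoint. Under 9.6.2.4 it is reported as a proportion with an exact binomial 95% CI.

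**The concern.** A subject with Grade 4 vomiting attributed to RAL meets the conditions of both 7.3 and 7.5. A subject with Grade 4 diarrhea attributed to RAL meets those of both 7.3 and 7.6. The general section ends the regimen; the event-specific sections start with symptomatic treatment and lead to a hold and restart. An investigator can cite either as the operative instruction.

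Two things are at stake. Subject protection at the most severe grade in these rules would depend on which paragraph the site happens to follow. And the permanent-discontinuation endpoint would partly record that choice rather than the tolerability of the regimen.

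**Working it through.** The protocol states no figure on this point, so there is none to reproduce. The check compares the texts and then sizes the effect on the endpoint.

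**1. Do the sections overlap?** Yes. Grade ≥ 3 in 7.5 and 7.6 includes Grade 4, and both are conditioned on attribution to RAL. Nausea, vomiting and diarrhea are symptomatic, so 7.3 applies as well.

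**2. Do they ask for the same thing at Grade 4?**

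| | 7.3 | 7.5 | 7.6 |
|---|---|---|---|
| First step | Discontinue | Antiemetics | Antidiarrheals, once infection is excluded |
| If not improved | not applicable | Hold optional (may) | Hold expected (should) |
| Restart | Stated only if RAL was not the cause | Foreseen | Foreseen |
| Recurrence, or more than 14 days | not applicable | Discontinuation optional | Discontinuation expected |

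They differ at the first step and on restart. Restart in 7.5 and 7.6 is inferred from their reference to recurrence on reinstitution of RAL.

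**3. Does any clause set precedence?** Only 7.2 has one, and it concerns Grade 3. Section 7.0 there plausibly means the whole chapter: 9.5 refers to Section 7.0 for subject management, and section 7.0 of the A5249s substudy does so for its whole toxicity plan. Read that way, the clause lets the event-specific sections displace the Grade 3 stop. It sits in the sentence on the initial stop, so whether it also reaches the later sentence on recurrence within 4 weeks is unclear. It does not reach 7.3.

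**4. Is the Grade ≥ 3 grouping visibly a deliberate exception to 7.3?** The text does not say. Where Grade 4 is treated separately, the result agrees with 7.3: 7.4.3 discontinues for Grade 4 rash, and 7.7.2 permanently discontinues for symptomatic Grade 4 AST/ALT elevation suspected to be due to the ARVs. Sections 7.5 and 7.6 do not separate Grade 4.

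**5. Is 8.1 complete?** No. It cites 7.1-7.3, but 7.7.2 (certain AST/ALT elevations) and 7.9 (confirmed CrCl below 50 mL/min) also mandate permanent discontinuation.

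**6. Size on the endpoint.** Assume n = 34 treated subjects (the accrual target in 9.4). Let x be the number whose status turns on which section is followed, with no other discontinuations. The exact limits are Beta quantiles: lower = B(0.025; x, n − x + 1), upper = B(0.975; x + 1, n − x). The values of x are assumptions.

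| x | x/34 | Exact 95% CI |
|---|---|---|
| 0 | 0.0% | 0 to 10.3% |
| 1 | 2.9% | 0.1 to 15.3% |
| 2 | 5.9% | 0.7 to 19.7% |
| 3 | 8.8% | 1.9 to 23.7% |

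**7. Effect on the as-treated sets.** Under 9.1, any missed dose on days 0-14 triggers replacement and as-treated exclusion, so a stop and a hold have the same consequence there. They differ only if dosing continues without a miss on symptomatic treatment. From day 57, a hold of up to 7 cumulative days keeps the subject in the as-treated set, while a discontinuation does not.

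**The case against.** **The specific section governs.** A sensible investigator might assume that a symptom-specific section overrides the general one. The protocol supports that, at most, for Grade 3 through 7.2. For Grade 4 it is left to assumption.

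**Discontinued in 7.3 need not mean permanently.** The protocol writes permanently in 7.2, 7.7.2 and 7.9, and 7.4 describes a discontinuation that lasts until symptoms resolve. The second paragraph of 7.3 speaks of Grade 4 events that require permanent discontinuation, which suggests that not all do. This stands: permanence is an inference, drawn from the resumption sentence and from 8.1. Even on the temporary reading, 7.3 requires a stop where 7.5 makes a hold optional ("the regimen may be held until Grade ≤ 2"). For persistent diarrhea the gap is narrower, because 7.6 says the regimen should be held.

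**There is oversight.** The core team must be told of toxicities that change or end the regimen, 7.5 and 7.6 involve it at the discontinuation step, and the TSMC reviews toxicity monthly. This makes unnoticed divergence less likely but does not say which rule applies.

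**Stronger readings that the text does not support:**
- A reader might infer a definite second conflict for recurrent Grade 3 nausea between 7.2 and 7.5. Because the 7.2 exception may carry over to recurrence, this is an ambiguity only.
- A reader might infer that choosing a stop or a hold on days 0-14 decides replacement and entry to the d1 analysis. Both mean missed doses, so it does not.
- A reader might take the 11% nausea and 7% diarrhea rates in 2.1 as a guide to frequency. They are for drug-related events of any grade, most of them mild to moderate, in a trial that reported no serious AEs. They give no Grade 4 rate.

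**Conclusion.** The point holds for Grade 4 nausea/vomiting and diarrhea attributed to RAL: 7.3 cannot be followed together with 7.5 or 7.6, and no clause resolves the overlap. The recurrence sentence in 7.2 is unclear rather than contradictory, and the 8.1 cross-reference is incomplete.

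The expected number of affected subjects cannot be estimated from the protocol and may be zero. If such a case occurs, it moves the permanent-discontinuation proportion by 2.9 percentage points. That assumes 34 treated subjects and the permanent reading of 7.3; accrual of replacements would make each case slightly smaller. The planned d1 sample size and precision are not shown to change. The weight of the point lies in consistent subject protection and in the meaning of a descriptive safety endpoint.

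**What to change.** - Reconcile 7.3 with 7.5 and 7.6 by stating which section governs at each grade. This can be a precedence sentence in 7.3 or an explicit grade range in 7.5 and 7.6.
- In 7.2, name the sections meant by the exception and say whether it also covers the recurrence sentence.
- State in 7.3 whether the discontinuation is permanent, so that the 9.2.2.4 endpoint can be counted in one way.
- Extend the 8.1 cross-reference to every section that mandates permanent discontinuation, including 7.7.2 and 7.9.

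Which clinical rule holds is for the protocol team to decide. The cost is a wording change by amendment, with no added data, visits or procedures.
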